### Study design and settings

2.1

This study will be a single-blinded, randomized controlled trial with 2 parallel groups. It will be conducted at North China University of Science and Technology-affiliated hospital. This protocol was written and based on Standard Protocol Items: Recommendations for Interventional Trials guidelines. If they agree, they will sign an informed consent form. Only those participants who read and agree to the protocol and who sign the informed consent form will take part of the study, following the schedule described in Figure 1.

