#### Inclusion criteria

2.3.2

Time of onset: last appeared to be normal until symptoms will be found <12 hours and >4.5 hours;The patient was found to be awake or witnesses found neurological deficits;NIHSS score ≥4 points;No changes or early changes are insufficient to the one-third distribution area of the middle cerebral artery;DWI/FLAIR imaging performance mismatch (DWI imaging and FLAIR imaging);All other indications for intravenous thrombolysis;Patients with large vessel occlusion are treated with endovascular treatment. The treatment principles refer to “Chinese Expert Consensus on Intravascular Treatment of Acute Ischemic Stroke.”

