#### Grouping method

2.4.2

We will be divided into awakening stroke group (wake group whose morbidity is not exact) and ischemic stroke group (the group clarifying the time of onset) according to whether the onset time of the patient is clear. The awakening group is divided into the awakening group with thrombolytic therapy and the awakening group without thrombolysis according to whether they receive thrombolytic therapy.

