#### Treatment solutions

2.5.2

Patients in the defined time-onset group will be given intravenous thrombolysis. The awakening group performs multimodal magnetic resonance imaging (MRI) screening (DWI and FLAIR) on the basis of meeting the pre-set conditions. If the MRI indicates that the DWI-FLAIR does not match, intravenous thrombolytic therapy will be given; if the MRI shows DWI-FLAIR matching, it will be given general treatment. Intravenous thrombolysis uses rt-PA. One-time dosage is 0.9 mg/kg, and the maximum dose does not exceed 90 mg. First, a 10% dose of intravenous bolus was given, and the rest of the dose continued to be infused intravenously for a total of 60 minutes. Thrombolysis is completed in the intensive care unit of the neurology department. During the thrombolysis process, the patient's consciousness and changes in limb muscle strength are closely observed. During this period, we will monitor patients’ vital signs, blood oxygen saturation, and give them treatments such as free radical scavenging and stable plaque. Recheck the computed tomography (CT) of the brain after 24 hours. If no intracranial hemorrhage is found, antiplatelet aggregation treatment (0.1 g oral aspirin tablets) should be given, and acupuncture and rehabilitation should be given after the condition is stable. Patients in the WUS group without thrombolysis received aspirin 300 mg orally as soon as possible after admission, and then changed to 100 mg/day. Other treatment methods will be the same as those of thrombolytic therapy.

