### Randomization and blinding

2.7

The concealment of random schemes: After the scheme design is completed, the random schemes are packed into sealed, light-tight envelopes encoded in sequence; then they are handed over to the person in charge of the project, and the qualified cases are selected before opening the envelope to determine case grouping.The recorder fills in the case report form with basic data and observation of local and systemic symptoms of the patient.We will make all kinds of documents in a unified wayCheck and confirm the correctness and completeness of all research data records and reports and case report forms, and ensure consistency with the original data.

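### The trial is called randomised, but onset type, MRI result and treatment received already fix every patient's group, so the plan gives no randomised estimate of thrombolysis in wake-up stroke

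*Protocol article*

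**What the plan says.** All references are to the protocol article.

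- **Design (2.1, repeated in the abstract):** "This study will be a single-blinded, randomized controlled trial with 2 parallel groups".
- **Allocation (2.7):** random schemes are placed in sealed envelopes in sequence, and "the qualified cases are selected before opening the envelope to determine case grouping".
- **Grouping method (2.4.2):** the first division is made "according to whether the onset time of the patient is clear". The wake-up group is then split into a thrombolysed group and "the awakening group without thrombolysis according to whether they receive thrombolytic therapy".
- **Treatment solutions (2.5.2):** "Patients in the defined time-onset group will be given intravenous thrombolysis". For wake-up patients, "If the MRI indicates that the DWI-FLAIR does not match, intravenous thrombolytic therapy will be given"; otherwise, "if the MRI shows DWI-FLAIR matching, it will be given general treatment".
- **Inclusion criteria (2.3.2):** the list includes "DWI/FLAIR imaging performance mismatch (DWI imaging and FLAIR imaging", and does not say that this applies to only some of the groups.
- **Aim (end of the Introduction):** to observe the efficacy of intravenous thrombolysis in wake-up stroke patients.
- **Statistical analysis (2.8):** the between-group comparisons named are unadjusted (t test, Mann-Whitney, chi-square, Fisher).

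**The concern.** Randomisation means that, for at least some patients, chance decides the group. Sections 2.1 and 2.7 say that it does. Sections 2.4.2 and 2.5.2 say that onset type, the MRI result and the treatment received decide it. Both descriptions cannot hold for the same patients.

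The efficacy aim is what suffers. A contrast of thrombolysed with non-thrombolysed wake-up patients is the natural way to address it. Under the MRI rule, that contrast compares two kinds of patient as well as two treatments. The article's Discussion treats mismatch as a sign of onset within about 3 to 4.5 hours, so by its own reasoning the two wake-up groups differ in how old the stroke is. Readers rely on the word randomised to rule out differences of that kind. Defining groups by treatment received would also forfeit the protection of randomisation even if an envelope had been opened.

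**Working it through.** The article states no sample size, power, effect size or allocation ratio, so there is no figure to reproduce. The check is structural.

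**Step 1: is anything left for the envelope to decide?** Section 2.5.2 gives:

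| Patient type | MRI result | Treatment | Decided by |
|---|---|---|---|
| Known onset | not specified | rt-PA | onset type |
| Wake-up | mismatch | rt-PA | MRI |
| Wake-up | match | general treatment | MRI |

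Every row has one treatment. Onset type cannot be allocated, and in the wake-up rows the MRI result settles treatment. No cell remains in which an envelope could send similar patients to different groups.

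**Step 2: does the wake-up comparator exist?** The answer depends on how the mismatch criterion in 2.3.2 is read.

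*Reading A: the criterion binds wake-up patients.* Then every enrolled wake-up patient has mismatch and, by 2.5.2, receives rt-PA. The matched, non-thrombolysed group contains no eligible patients, and there is no contrast to analyse.

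*Reading B: the criterion does not bind them.* Let T = 1 for thrombolysis and M = 1 for mismatch. Section 2.5.2 sets

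- P(T = 1 | M = 1) = 1
- P(T = 1 | M = 0) = 0

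so T = M for every wake-up patient and their correlation is 1.0. In a model with columns (intercept, T, M), the last two columns are identical. A numerical check with 50 patients of each MRI status gave rank 2 of 3 columns. The rank would be the same at any sample size.

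**Step 3: what would the contrast estimate under Reading B?** Let a be the effect of rt-PA in mismatch patients, and b the difference in outcome between mismatch and matched patients if neither were thrombolysed. The expected difference between the two wake-up groups is

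mean(T = 1) − mean(T = 0) = a + b.

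Only the sum can be estimated. Regression adjustment and matching need patients with the same M and different T, and there are none. A larger sample estimates a + b more precisely but does not isolate a.

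**Step 4: can the other contrast stand in?** Wake-up thrombolysed versus known-onset thrombolysed is defined by onset type, so it is not randomised either. Both groups receive rt-PA, so it holds no information about thrombolysis against no thrombolysis. Section 2.5.2 specifies DWI and FLAIR screening only for the wake-up group, so the text does not show that MRI status would be available for adjustment in the known-onset group.

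**The case against.** **The envelopes might allocate treatment among mismatch patients, and the flow chart may show this.** The study flow chart (Figure 2) is not reproduced in the text available. Such allocation would remove the confounding. However, 2.5.2 says that mismatch patients are thrombolysed, without qualification, and 2.4.2 groups by treatment received. A figure showing another scheme would add to the conflict in the text. A separate analysis plan could not create a random step that the treatment rule excludes.

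**An article condenses the full protocol.** That would answer a complaint about missing detail. Here the difficulty is statements that are present and incompatible.

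**The confounding is conditional.** This stands. A reader might infer that the two wake-up groups are fully confounded whatever the eligibility rule. That follows only if the mismatch criterion is not applied to wake-up patients. If it is applied, the fault is an empty comparator.

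**The size of any bias is unknown.** This also stands. A reader might infer that mismatch patients would do better untreated and that the trial must therefore overstate the benefit. The article links mismatch to recent onset but gives no untreated outcome by MRI status. The 36.4% with mRS of 1 or below in its Discussion comes from a cited study of thrombolysed patients. Neither the direction nor the size of b can be taken from the document.

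**The number of groups.** Section 2.4.2 yields three final groups, but two parallel groups can fairly mean the top-level division into wake-up and known onset. The count alone proves little; the missing random step is the issue.

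**Other aims.** The abstract and Introduction also plan to assess onset time and compare imaging characteristics. That aim needs no randomised contrast and is not undermined by this point.

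**Conclusion.** The point holds in conditional form. As written, the plan claims a property, randomisation, that its own grouping and treatment rules leave no room for. The wake-up comparison is either empty (mismatch required) or unidentifiable (mismatch not required: rank 2 of 3, no overlap on MRI status). On both readings, the efficacy of thrombolysis in wake-up stroke is not estimated by randomisation.

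This rests only on 2.5.2 being followed as stated. It needs no assumed outcome rate or sample size, and no numerical bias is claimed. The documents do not support the stronger inferences that the whole study is void, or that a spurious benefit will be reported as a randomised result: the Discussion itself says that a statistically significant benefit has yet to be shown. The correction is nevertheless needed before enrolment, because no later analysis can supply the missing random step.

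**What to change.** Reconcile the abstract's design statement with sections 2.1, 2.3.2, 2.4.2, 2.5.2 and 2.7, and make Figure 2 agree with the result. Two routes are open.

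1. **If the trial is randomised:** state what is randomised, in whom and between which groups. Say which patients the mismatch criterion applies to. Define the analysis groups by allocation, not by treatment received.
2. **If grouping follows onset type and MRI:** delete the word randomized and the envelope text, and describe a non-randomised cohort study. State that the thrombolysed versus non-thrombolysed wake-up comparison does not estimate the effect of thrombolysis. Present any comparison of wake-up with known-onset patients among the thrombolysed as descriptive of onset type, not as evidence of efficacy.

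The second route costs a wording change in the protocol and, where it carries the same label, in the registration, plus a weaker claim. The first needs a protocol amendment with ethics review before enrolment starts. Which treatment rule is right is for the investigators to decide; the request is only that the sections agree and that the claim matches the design.

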### Outcome measures

2.6

#### Safety evaluation after thrombolysis

2.6.1

The occurrence time, treatment measures, and results of various adverse events such as intracranial hemorrhage, skin, gums, and digestive tract in patients undergoing thrombolytic therapy are recorded by specialized personnel. The safety of thrombolytic therapy is mainly evaluated by the incidence of intracranial hemorrhage. During thrombolysis, if there is headache, vomiting, and other suspected intracranial hemorrhage or other parts of the bleeding, stop thrombolysis immediately. At the same time, review the head CT. If there is no symptom of appeal, the head CT is reviewed 24 hours after thrombolysis. The significant deterioration of nerve function caused by intracranial hemorrhage (increased NIHSS score ≥4 points) will be considered as symptomatic intracranial hemorrhage.

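### Dedicated bleeding records and follow-up CT are specified only for thrombolysed patients, so the plan yields no bleeding rate for wake-up stroke patients who are not thrombolysed

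*Protocol article*

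**What the plan says.** Section 2.6.1 of the protocol article covers safety after thrombolysis. It lists bleeding in the head, skin, gums and digestive tract and says that such events "in patients undergoing thrombolytic therapy are recorded by specialized personnel". It names the main measure: "The safety of thrombolytic therapy is mainly evaluated by the incidence of intracranial hemorrhage".

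The imaging rules in the same section follow the thrombolysis course. If bleeding is suspected during the infusion, the instruction is "At the same time, review the head CT". Otherwise "the head CT is reviewed 24 hours after thrombolysis".

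Symptomatic haemorrhage is defined once, in that section: "The significant deterioration of nerve function caused by intracranial hemorrhage (increased NIHSS score ≥4 points) will be considered as symptomatic intracranial hemorrhage".

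Section 2.4.2 splits the wake-up group by whether thrombolysis is given, and section 2.5.2 describes the untreated part: "Patients in the WUS group without thrombolysis received aspirin 300 mg orally as soon as possible after admission". It then adds: "Other treatment methods will be the same as those of thrombolytic therapy".

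Two other places touch on safety without naming a group. Section 2.7 has the recorder enter "observation of local and systemic symptoms of the patient" on the case report form. Section 2.6.2 plans NIHSS at admission, 24 hours and 7 days, and counts death, like a 4-point rise, as an unfavourable result.

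**The concern.** Safety is a large part of why thrombolysis in wake-up stroke is disputed. The Abstract and Discussion both call its safety an open question, and the Discussion says that treatment beyond the time window raises the rate of symptomatic intracranial haemorrhage. The useful safety question is therefore how much more bleeding thrombolysis causes in wake-up stroke than no thrombolysis.

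That needs a bleeding rate on both sides. Patients on aspirin can bleed, and an infarct can turn haemorrhagic without thrombolysis. If only the thrombolysed side has a dedicated record, the whole of its observed rate may be attributed to thrombolysis. Empty fields in the comparator may also be read as zero events.

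**Working it through.** No arithmetic on event rates is possible, because the article gives no sample size, haemorrhage rate or margin for safety. The check is to set the sections side by side.

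**Step 1: which groups have planned ascertainment.**

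| Group (2.4.2, 2.5.2) | Dedicated bleeding record (2.6.1) | Scheduled follow-up CT (2.5.2, 2.6.1) | NIHSS and death (2.6.2) | General symptoms (2.7) |
|---|---|---|---|---|
| Known onset, thrombolysed | yes | yes | yes | yes |
| Wake-up, thrombolysed | yes | yes | yes | yes |
| Wake-up, not thrombolysed | not specified | not specified | yes | yes |

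Two of three groups have a dedicated bleeding record.

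**Step 2: which contrasts can be formed.** Let p(WT), p(WN) and p(KT) be the bleeding rates in wake-up thrombolysed, wake-up non-thrombolysed and known-onset thrombolysed patients.

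- Thrombolysis against none in wake-up stroke: p(WT) − p(WN). Only the first term has planned ascertainment, so the difference cannot be formed from the planned safety data.
- Wake-up against known onset, both thrombolysed: p(WT) − p(KT). This can be formed, but it asks whether wake-up patients bleed more under the same treatment, not what thrombolysis adds.

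**Step 3: whether other text closes the gap.**

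- The carry-over sentence in 2.5.2 concerns treatment methods, not event recording. The 24-hour CT in that section is the check made before antiplatelet treatment after thrombolysis. The non-thrombolysed group starts aspirin soon after admission, so that check has no counterpart there.
- The symptom entry in 2.7 does not name bleeding and is not linked to CT.
- NIHSS and death in 2.6.2 would show that a patient worsened, but not that haemorrhage was the cause.

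**Step 4: the symptomatic definition.** It has two parts: deterioration caused by intracranial haemorrhage, and an NIHSS rise of at least 4 points as the severity threshold. It does not mention death, whereas the worsening rule in 2.6.2 does. With NIHSS planned at three time points, a patient who dies of haemorrhage between two of them may have no scored rise, which leaves the symptomatic label unclear. The patient still counts in the main measure, which is any intracranial haemorrhage.

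**Step 5: what equal recording would and would not give.** Write the detected rate of any intracranial haemorrhage as (clinically triggered) + (found only on scheduled CT). The second part exists only where that CT is scheduled, so comparing any haemorrhage would count silent bleeds on one side only. The first part can be sought in the same way in all groups.

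**The case against.** The strongest reply is that this is a condensed article. Section 2.6.1 describes what is done for thrombolysed patients and nowhere says that events in others go unrecorded. The assessment schedule (Figure 1) and the flow chart (Figure 2) are not shown, and the full protocol may contain a common adverse event form. It is also true that the symptom record, NIHSS and death are not limited to one group, and that the carry-over sentence could be read generously enough to include the 24-hour CT.

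Part of this stands. A reader might infer that nothing at all is recorded in the non-thrombolysed group; the article does not support that. Nor can the text shown rule out fuller recording elsewhere. But section 2.6.1 does more than stay silent: it names the population in which bleeding is recorded, and nothing shown widens it.

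Three other readings are tempting and fail:

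- That symptomatic haemorrhage rests on an NIHSS rise alone. The definition requires that haemorrhage caused the deterioration, and head CT is provided for. The definition is also not the reason why the comparison is missing.
- That fatal haemorrhages in thrombolysed patients are lost. The main measure is any intracranial haemorrhage, and the result of each event is recorded. Only the symptomatic label is unclear.
- That equal recording would by itself give the excess harm of thrombolysis. Section 2.5.2 gives thrombolysis on DWI-FLAIR mismatch and general treatment on match, so the groups would differ in more than treatment.

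**Conclusion.** The point holds for ascertainment. As written, dedicated bleeding records and follow-up CT cover two of three groups, and the omitted group is the only non-thrombolysed one. Bleeding with thrombolysis therefore cannot be compared with bleeding without it in wake-up stroke from the planned safety data. No numerical size can be attached, since the article gives no rates or numbers of patients.

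The conclusion rests on the text shown and assumes that the missing figures and any fuller protocol do not extend the recording. If they do, section 2.6.1 needs only to be brought into line with them. The omission of death from the symptomatic definition is a lesser point of consistency with 2.6.2. The confounding that follows from allocation by DWI-FLAIR result is a separate problem. It limits what the repaired comparison can show, but is no reason to leave one group without a bleeding record.

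**What to change.** Change section 2.6.1 as follows:

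1. Record the same bleeding events, and any intracranial haemorrhage found on clinically indicated CT, in all groups over the same period, from admission to day 7.
2. Use one definition of symptomatic haemorrhage in all groups: deterioration caused by intracranial haemorrhage with an NIHSS rise of at least 4 points, or death from it. This brings 2.6.1 into line with 2.6.2.
3. Base the between-group comparison on this clinically triggered endpoint. Report haemorrhage found only on the scheduled 24-hour CT separately, for the groups that have that CT.
4. State that the contrast is descriptive and confounded if thrombolysis is assigned by DWI-FLAIR result as in 2.5.2. That allocation must be reconciled with the sealed-envelope randomisation in 2.7.

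The cost is case report form pages for the non-thrombolysed group, revised wording and a little more recording work. NIHSS at 24 hours and 7 days is already planned without restriction by group, and no extra scheduled CT or change of treatment is needed. One limitation remains: detection of asymptomatic haemorrhage stays unequal between the groups, and the report should say so.

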#### Evaluation of efficacy and prognosis

2.6.2

A trained neurologist who will be unaware of the patient's morbidity was evaluated by the National Institutes of Health Stroke Scale (NIHSS score) at the time of patient admission, 24 hours after treatment, and 7 days after treatment. After discharge, the patient's prognosis was evaluated by the modified RanKin scale (mRS). We defined mRS score 0 to 1 points as cured and 0 to 2 points as good prognosis. After 7 days of treatment, the NIHSS score is reduced by 4 points and it is considered that it will be judged as effective in the early stage, and the NIHSS score is increased by 4 points or death will be judged as invalid or worse (Table 1).

**Table 1 T1:**
[figure not shown]
National Institutes of Health Stroke Scale.

### Randomization and blinding

2.7

The concealment of random schemes: After the scheme design is completed, the random schemes are packed into sealed, light-tight envelopes encoded in sequence; then they are handed over to the person in charge of the project, and the qualified cases are selected before opening the envelope to determine case grouping.The recorder fills in the case report form with basic data and observation of local and systemic symptoms of the patient.We will make all kinds of documents in a unified wayCheck and confirm the correctness and completeness of all research data records and reports and case report forms, and ensure consistency with the original data.

